## Abstract

**Background:**

There is little evidence of whether or not those who have attended cardiac rehabilitation (CR) are meeting the physical activity guidelines recommended for secondary prevention of cardiovascular disease. In healthy individuals, there is evidence, that even if individuals are meeting the physical activity guidelines, the harmfulness of too much sedentary behaviour remains (active couch potato (ACP) phenomenon). Currently, there appears to be no evidence of the ACP phenomenon in those attending CR. The aims of the study are to examine the level of physical activity and sedentary behaviour in those with coronary heart disease (CHD) who have attended CR, and to investigate the potential independent associations between these behaviours and cardio-metabolic health, health-related quality of life, exercise capacity, anxiety and depression.

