## Background

Heart disease is the leading single cause of death of men and women in Australia, and is prevalent worldwide [1, 2]. It is estimated that 34 % of all heart attacks in Australia are repeat events [3]. Not only are repeat cardiac events more likely to be fatal, they result in a higher burden of disease cost than initial events, with the total economic cost of repeat cardiac events in Australia amounting to $8.4 billion in 2010 [3].

Internationally, it is recommended that all those with coronary heart disease (CHD) be offered cardiac rehabilitation (CR), a secondary prevention program. It is widely recognised that CR decreases mortality, improves risk profiles, decreases hospital admissions, increases medication adherence and improves quality of life [4–7]. CR programs are usually exercise-based, consisting of either regular exercise alone, or a combination of exercise with education and psychological support. Moderate-intensity aerobic exercise, or physical activity, is considered a core component of CR [5, 8]. CR participants are encouraged to increase their moderate-intensity aerobic physical activity slowly and gradually, aiming to accumulate a minimum of 30 min on most, or all, days of the week, throughout life [8]. However, little is known about how much physical activity these individuals undertake outside of the CR program. It is not clear whether CR participants’ are meeting the physical activity guidelines as recommended for secondary prevention, with some indication that only 8.4 min per day of moderate-to-vigorous intensity physical activity (MVPA) is achieved in the first 12 months following diagnosis of CHD [9–11].

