In healthy individuals, there is evidence that even if you do enough physical activity to meet the recommendations, by sitting too much (sedentary behaviour), the harmfulness of too much sitting time remains (the ‘active couch potato’ (ACP) phenomenon) [12]. The few prospective studies that have attempted to research this phenomenon have reached the same conclusion: meeting the public health guidelines regarding physical activity (150 min moderate-to-vigorous intensity aerobic physical activity per week) may not necessarily protect against the possible harmful effects from excessive sedentary behaviour [12, 13]. It appears that the more sedentary you are, the more likely you are to die from any cause, with sedentary behaviour recently being considered an independent risk factor for cardiovascular disease and all-cause mortality [14–16]. There is also some evidence that those with cardiovascular disease or diabetes are more likely to die from any cause if they sit for too long, independent of physical activity [17]. Therefore, it is important to take into consideration sedentary behaviour when working towards secondary prevention in those with CHD, intending to prevent further cardiac events.

To our knowledge there are limited studies assessing the effect of physical activity on health outcomes in people with CHD, with no identified studies assessing the effect of sedentary behaviour [18]. The general aim of the current study is two-fold: a) to assess the physical activity levels and sedentary behaviour (ACP phenomenon) outside the clinic in participants attending a hospital-based phase II CR program over 12 months, b) to assess the potential, independent risk of this behaviour on the cardio-metabolic health, health-related quality of life, exercise capacity, anxiety and depression of CR participants.

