### Statistical analysis

The number of minutes per day spent in sedentary behaviour will be calculated using standard count-based intensity threshold values of counts per minute: < 100 for sedentary behaviour (<1.5 MET). Four further summary measures of sedentary behaviours will calculated per day and averaged over valid days: (a) percentage of the wear-day spent in sedentary behaviour (b) number of sedentary bouts (defined as a period of consecutive minutes where the accelerometer registered <100 counts/minutes) (c) average duration of sedentary bouts and (d) number of sedentary breaks (defined as at least 1 min where the accelerometer registered ≥ 100 counts/minute following a sedentary bout). The Freedson Combination energy expenditure algorithm will be used to determine the intensity cut-points for MVPA. This outcome variable will be used to investigate whether participants have reached the World Health Organisation physical activity guidelines.

Linear regression models will be performed at each data collection point, where the dependent variables will be each of the health variables available. The models will have the different summary measures of sedentary behaviour (i.e. one model will be performed with each one) as main independent variables, and models will also be performed for MVPA and each of the different physical activity intensities (i.e. light, moderate and vigorous physical activity). If it is the case, quadratic trends might be explored. The models will be adjusted for total time of activity (i.e. counts per min ≥ 100), gender, socioeconomics variables, BMI and other potential confounders available.

Additional analyses will be completed with a one-way repeated measures analysis of variance (ANOVA) to test for differences in physical activity and sedentary behaviour (with a 95 % confidence interval (CI)) within the Australian sample over 12 months. Intention-to-treat analysis will be used at 6-weeks, 6 and 12-months where data is missing, bringing the last value forward. A maximum of three attempts will be made to contact participants so outcome measures can be obtained, making the analysis more complete.

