## Discussion

Over 12 months we will assess the physical activity, sedentary behaviour levels and health outcomes of those with CHD attending a hospital-based phase II CR program. Specifically, we will measure the physical activity and sedentary behaviour levels of participants’ with CHD at the start of a phase II CR program, at the end of the program, and at 6 and 12-months to determine the short and medium-term changes in physical activity and sedentary behaviour levels. Few studies have determined whether those attending CR achieve the public health physical activity guidelines, as recommended, over the short and medium term, and no known studies have reported on CR participants’ sedentary behaviour, or sitting time. Importantly, we will also investigate the relationships between physical activity, sedentary behaviour and health outcomes at each point-in-time to determine the potential, independent risk of these behaviours, including the potential for the ACP phenomenon in CR participants.

One of the strengths of the trial is the pooling of baseline results from multiple sites, internationally. Combining data will increase the strength of statistical power analyses, with the sample size to be recruited providing adequate statistical power to detect relationships between the variables. The Australian single cohort study is prospective, allowing all the relevant information to be collected, including the objective and subjective measurement of physical activity and sedentary behaviour. The outcome measures are also collected in a ‘real-world’ situation, reflecting common practice for CR in Australia.

Limitations to the study include multiple assessors of outcome measures despite assessors remaining consistent for each outcome measure, for example, exercise capacity will always be assessed by an exercise physiologist. There is also a lack of randomisation, with recruitment of participants occurring consecutively. Other possible limitations include the potential for loss of participants to follow-up, and few participants achieving the outcome of interest, the ACP phenomenon.

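### The planned models estimate one sedentary slope over all participants, but the active couch potato (ACP) question concerns only those who meet the activity guideline

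*Protocol article*

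**What the plan says.** The Background of the Protocol article introduces ACP, for healthy people, as a conditional statement: "even if you do enough physical activity to meet the recommendations, by sitting too much (sedentary behaviour), the harmfulness of too much sitting time remains". It gives the guideline as "150 min moderate-to-vigorous intensity aerobic physical activity per week". The Discussion says the relationships between activity, sedentary behaviour and health will be examined at each time point to judge independent risk, "including the potential for the ACP phenomenon in CR participants".

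Under Statistical analysis the regressions are set out as follows: "The models will have the different summary measures of sedentary behaviour (i.e. one model will be performed with each one) as main independent variables". They are adjusted for total time at 100 counts per minute or more, gender, socioeconomic variables, BMI and other available confounders, and quadratic trends are optional. MVPA is used to see who reached the guideline, and no other use of guideline status is stated. The section names no interaction with guideline status, no stratum and no restriction to meeters.

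Two statements bear on how many meeters to expect. The Background reports some indication that "only 8.4 min per day of moderate-to-vigorous intensity physical activity (MVPA) is achieved" in the first year after diagnosis. The Discussion lists as a possible limitation "few participants achieving the outcome of interest, the ACP phenomenon".

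**The concern.** ACP, as described, is a statement about the sedentary–health association among people who meet the guideline. The planned coefficient is an average association over meeters and non-meeters. Adjusting for activity does not turn one into the other: a covariate deals with confounding, but it does not let the sedentary slope differ by guideline status. A quadratic term in sedentary time does not do so either.

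If the two groups differ, the pooled slope can mislead about ACP in both directions. An association present only in inactive patients, in whom ACP cannot occur by definition, can produce a significant pooled slope. An association confined to meeters can be diluted until it is missed. The ACP conclusion is what is at stake; the description of activity levels and the general association are not affected.

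**Working it through.** **1. The plan's own sample size.** Inputs from Sample size: f² = 0.5, 10 predictors, α = 0.05, power 0.95. The omnibus F test has 10 and N − 11 degrees of freedom and noncentrality 0.5 × N. Power is 0.947 at N = 58 and 0.952 at N = 59 (noncentrality 29.5), so 59 reproduces. It is sized for all ten predictors jointly and gives no assurance about a slope in a subgroup.

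**2. How common meeters may be.** 8.4 min/day × 7 = 58.8 min/week, against 150. This suggests that meeters may be a minority. It is a level taken from cited work, not a distribution for this cohort, so the share of meeters has to be assumed.

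**3. What the pooled slope estimates.** With a share p of meeters, the pooled slope is roughly p × (meeters' slope) + (1 − p) × (non-meeters' slope).

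- Slope 0 in meeters and 0.4 in non-meeters: 0.9 × 0.4 = 0.36, 0.8 × 0.4 = 0.32 and 0.7 × 0.4 = 0.28 at p = 10, 20 and 30%.
- The reverse, 0.4 in meeters only: 0.04, 0.08 and 0.12.

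**4. Simulation of the first case at n = 59.** None of these assumptions is in the protocol: standardised sedentary time, residual SD 1, sedentary–MVPA correlation −0.3, an activity covariate plus seven further covariates, and a two-sided test at 5%. The planned covariate is total time at 100 counts per minute or more. Together with sedentary time it makes up wear time, so a strong negative correlation is plausible; −0.7 to −0.95 was used. MVPA adjustment is shown for comparison.

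| Pooled slope significant | 10% meeters | 20% | 30% |
|---|---|---|---|
| Adjusted for MVPA | 63% | 54% | 45% |
| Adjusted for total activity, correlation −0.7 | 38% | 33% | 25% |
| Adjusted for total activity, correlation −0.95 | 12% | 10% | 9% |

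The slope estimated in meeters, from a model with guideline status and its interaction with sedentary time, is significant in 4–6% of samples.

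**5. Precision of the meeters' slope.** At n = 59 the 95% CI half-width is about 0.6 (30% meeters) to 1.0 (10% meeters) SD per SD with MVPA adjustment, and wider with total-activity adjustment. In a separate set of runs with a true slope of 0.5 in everyone, power for the meeters' slope was about 22, 42 and 60% at 15, 30 and 50% meeters, against about 87% for the pooled slope.

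**The case against.** The case on the other side has four parts.

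- **No ACP hypothesis or decision rule is stated.** The aims speak of independent associations, and a pooled adjusted slope is a conventional answer to them. This stands. The models should stay, and the point is limited to ACP.
- **ACP is also used descriptively,** as a status that a participant may have. The planned derivation of sedentary time and guideline attainment serves that use. This stands too, but the Discussion also ties ACP to the association analyses, and there the gap remains.
- **The article is condensed, and a separate analysis plan could add an interaction.** It could. But the article fixes the exposure terms and the adjustment set in some detail and attaches to these analyses a question that they do not answer as written.
- **The remedy is imprecise where meeters are few.** True: 10% of 59 is about six people. That argues for reporting ACP as undetermined in that cohort, not for reading it from non-meeters.

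A reader might infer that the plan carries a false-positive rate for ACP of half or more, or that it tests a stated ACP null wrongly. The documents support neither. In the simulated setting a true average association exists, so the pooled test rejects its own null correctly; the result misleads only if it is then read as ACP. The highest rates also come from MVPA adjustment, which is not the planned covariate, and from a complete difference between groups that the protocol does not assert.

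**Conclusion.** The point holds for the ACP question only. As written, the regressions give one slope over all participants, which bears on ACP only under the assumption that meeters and non-meeters share it, and that is the very matter in question.

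The direction follows from the text and from the weighted average. The size does not. In the assumed setting, a significant pooled slope with no association in meeters occurs in roughly 9–38% of samples under the planned type of adjustment and 45–63% under MVPA adjustment, against 4–6% for the meeters' slope. These figures depend on the assumed share of meeters, slopes and correlations, and should be read as illustration.

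**What to change.** In Statistical analysis:

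- Keep the whole-sample models and say that they address the general independent association.
- Add a version of each sedentary model with guideline status (met or not met, already derived) and its interaction with the sedentary measure.
- Report the sedentary slope with its 95% CI separately in meeters and non-meeters, and base any ACP statement on the meeters' slope and its interval.
- Name the pooled international baseline data as the main dataset for this contrast.

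The cost is two model terms and one reporting rule, with no new data. The two terms count against the stated maximum of 10 predictors. The international sample size is not given in the article, so the precision there cannot be promised. In the Australian cohort alone the meeters' slope will be imprecise, and ACP may have to be reported there as undetermined.

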**Methods:**

A prospective cohort study will be conducted in Australia over 12-months. Baseline data from this study will contribute to an international, multi-centre cross-sectional study (Australia, New Zealand, United States of America, South Africa, Spain, and Portugal). Adults currently enrolled in a 6-week phase II cardiac rehabilitation program with stable CHD and receiving optimal medical treatment +/− revascularisation will be recruited. Outcome measures will be taken at baseline (commence CR), 6 weeks (complete CR), 6 and 12-months. Physical activity and sedentary behaviour will be measured using accelerometry and two questionnaires (Active Australia Survey, Past-Day Adults’ Sedentary Time questionnaire). Health outcomes will include body mass index, waist-to-hip ratio, lipid profile, blood glucose level, quality-of-life (MacNew), exercise capacity (6-min walk test), anxiety and depression (Hospital Anxiety and Depression Scale).

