### Outcome measures

All study measures will be collected at baseline, 6-weeks, 6 and 12 months. All assessments will be conducted at the hospital where the CR program takes place, and will be carried out by a trained health professional. This excludes the blood samples, which will be collected at pathology collection centres. The PI will ensure that all assessors comply with data collection protocols to promote data quality and minimise measurement error.

The main outcome measures are sedentary behaviour and physical activity levels objectively measured using an accelerometer. Subjective measures of sedentary behaviour (Past-Day Adults’ Sedentary Time questionnaire, PAST) and physical activity (Active Australia Survey, AAS) have also been included in this study as they are commonly employed as outcome measures in the clinical setting due to their low cost and ease of use [19]. Haskell also suggests that physical activity data is best interpreted by adopting a combination of objective and subjective measures [20]. Dependent variables include body mass index (BMI), waist-to-hip ratio (WHR), blood lipid and glucose levels, exercise capacity (6-min walk test, 6MWT), quality of life (MacNew Heart Disease Health-related Quality of Life Questionnaire, MacNew) and anxiety and depression (Hospital Anxiety and Depression Scale, HADS).

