### Sample size

The G*Power software v.3.1.9.2 was used to *a priori* determine the required sample size. Previous recommendations for sample size estimation in Multiple Linear Regression problems were used [32]. With a desired effect size of f^2^ = 0.5 (large), given a maximum of 10 predictor variables including potential confounders, a sample size of *n* = 59 is needed to achieve a power of 0.95 in a test based on α = 0.05. Assuming a dropout rate of 25 %, 75 participants will be recruited for the Australian study.

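### BMI is both a dependent variable and a covariate with no stated exception, so the BMI models as written cannot estimate anything, and the role of BMI in the related models is left unsettled

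*Protocol article*

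**What the plan says.** Three statements in the protocol article bear on this point.

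- **BMI as an outcome.** The Outcome measures section states: "Dependent variables include body mass index (BMI), waist-to-hip ratio (WHR), blood lipid and glucose levels". The abstract agrees: "Health outcomes will include body mass index, waist-to-hip ratio, lipid profile, blood glucose level".
- **Which outcomes are modelled.** Under Statistical analysis, "the dependent variables will be each of the health variables available". BMI is not set apart.
- **Covariates.** The same paragraph gives one adjustment set for the models: total activity time, then "gender, socioeconomics variables, BMI and other potential confounders available". It gives no separate set for the BMI models and plans no version without BMI.

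On timing, "Linear regression models will be performed at each data collection point", and the Outcome measures section has all measures taken at each of the four visits. The natural reading is therefore that BMI from the same visit is the covariate. The aim that these models serve is given in the Background: "to assess the potential, independent risk of this behaviour on the cardio-metabolic health", together with quality of life, exercise capacity, anxiety and depression.

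**The concern.** The outcome list and the covariate list share a variable. Where that variable is the outcome, the written rule gives a model with no information about sedentary behaviour or physical activity, so one named health outcome has no usable analysis as specified.

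A second, softer issue comes from the same sentence. By listing BMI as a dependent variable, the protocol treats it as something the behaviours may influence. By adjusting for it, the protocol treats it as something that confounds the behaviours' associations with other outcomes. If BMI lies partly on the path from sitting to waist-to-hip ratio, lipids, glucose or walking distance, a BMI-adjusted coefficient leaves that part out, and a null value could be misread as no association. If BMI is a confounder, the adjustment is needed. The protocol does not say which it assumes.

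**Working it through.** **1. Count of the affected models.** The exposures come from the Statistical analysis section. There are five sedentary measures (minutes per day plus four further summaries) and four activity measures (MVPA, light, moderate, vigorous), with one model for each. That is 5 + 4 = 9. The visits are baseline, 6 weeks, 6 months and 12 months, so 4. BMI models: 9 × 4 = 36.

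**2. What the BMI model returns.** Write BMI = β₀ + β₁·exposure + β₂·BMI + other terms + error. Setting β₂ = 1 and all other coefficients to 0 fits every observation exactly. The residual sum of squares is 0 and R² = 1. Provided the covariates are not collinear, this is the only least-squares solution, so β₁ = 0 whatever the data.

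A simulated data set of 59 with an assumed exposure–BMI correlation of 0.4 (exposure, sex and BMI as predictors) shows this:

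| Model for BMI | Exposure coefficient | R² |
|---|---|---|
| BMI among the covariates | 0 | 1 |
| BMI omitted | 0.41 | 0.16 |

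**3. Effect of the fix on sample size.** The Sample size section states n = 59 for f² = 0.5, 10 predictors, power 0.95 and α = 0.05. The overall F test reproduces this: noncentrality 0.5 × 59 = 29.5, degrees of freedom 10 and 59 − 11 = 48, power 0.952, and 59 is the smallest n that reaches 0.95. Dropping BMI leaves 9 predictors. Then 57 suffice, and power at 59 is 0.962. The fix costs no participants.

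**4. The other outcomes: illustration only.** The documents give no coefficients, so all values here are assumed and standardised. Let d be the exposure–outcome coefficient given BMI, a the exposure–BMI association and b the BMI–outcome coefficient.

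- Without BMI in the model: d + a·b. With BMI: d.
- Share removed by adjustment: a·b / (d + a·b).
- With d = 0.1, a = 0.1 and b = 0.3: 0.03 / 0.13 = 23%.
- With d = 0.1, a = 0.4 and b = 0.5: 0.20 / 0.30 = 67%.
- With d = 0.1, a = 0.3 and b = 0.5: the coefficient falls from 0.25 to 0.10, or 60% removed. A large simulation gave 0.248 and 0.097.

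The arithmetic is the same if the arrow between exposure and BMI is reversed. If higher BMI leads to more sitting, a·b is confounding: 0.25 is the biased figure and 0.10 the right one. Data from a single visit give the same two coefficients in either case. The models also adjust for total activity time, so any exposure–BMI path would have to be read conditionally on that.

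**The case against.** The strongest reply is that this is a slip of wording in a condensed article. A variable cannot confound its own model, any analyst would drop BMI there, and nobody would report R² = 1 as a result. That is probably how it would go in practice, and it limits the harm. It does not remove the fault. The article does state a covariate rule, and that rule conflicts with its own outcome list, so this is not a detail left to a fuller document.

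On the other outcomes the reply is stronger. A reader might infer that the plan adjusts away a pathway the study sets out to estimate, and that its cardio-metabolic associations will be pulled toward the null by some known share. The documents do not support this. No section names a pathway through adiposity as a target. The Background speaks of independent risk, and an association independent of body size is a legitimate thing to estimate. Separate models at each visit cannot tell a mediator from a confounder, and a model without BMI would be the biased one if BMI is a confounder. The 23% to 67% range follows wholly from assumed inputs that share a sign. These objections stand, and they rule out insisting that the model without BMI be the main one.

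**Conclusion.** The conflict over BMI as outcome and covariate is certain from the text. As written, 36 models (9 exposures × 4 visits) can estimate no association between the behaviours and BMI. This rests on algebra alone.

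For waist-to-hip ratio, lipids, glucose and 6-minute walk distance, the finding is limited to this: the protocol gives BMI two roles and does not say how the adjusted results are to be read. Whether adjustment removes a real part of the association or removes confounding, and by how much, cannot be learned from the documents.

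The weight is moderate. The main outcome measures are accelerometer sedentary behaviour and physical activity. Their repeated-measures analysis, as described, does not involve BMI, and the sample size stands. A reader might go further and expect BMI to end with no reported result at all. That is unlikely, since the fault would show at the first model fitted, but the choice of covariates would then be made after the data were in hand.

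**What to change.** In the Statistical analysis section:

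1. State that BMI is omitted from the covariates when BMI is the dependent variable.
2. For waist-to-hip ratio, lipids, glucose and 6-minute walk distance, report each model with and without BMI. Name the primary version in advance with a sentence of reasoning (BMI as confounder or as possible intermediate), and label the other as a sensitivity analysis.
3. State that a null BMI-adjusted coefficient will not on its own be interpreted as no association.

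**Cost.** The first change is one clause. The second uses only data already planned for collection. Counting five lipid measures (triglycerides, total cholesterol, HDL, non-HDL, LDL), it covers 1 + 5 + 1 + 1 = 8 outcomes, so 8 × 36 = 288 further regressions. These are cheap to run but add output, which is a further reason to fix the primary version beforehand. No participants, visits or measurements are added.

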## Methods

### Design

A prospective cohort study will be conducted in an Australian hospital-based phase II CR program over 12-months. Baseline data from this study will contribute to an international, multi-centre cross-sectional study (Australia, New Zealand, United States of America, South Africa, Spain, and Portugal). At baseline, participants will be assessed within the first 2 weeks after enrolment in the phase II CR program. In Australia, participants will be assessed again within 2 weeks of finishing the 6-week phase II CR program, and at 6 and 12-months following admission into the phase II CR program. The phase II cardiac CR program included in this study is typical of most contemporary CR programs in Australia. The CR program is multidisciplinary, time-limited (twice a week, 6-weeks), conducted in groups, hospital-based, and has educational and supervised exercise components (one hour education plus one hour exercise) [4].

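### The repeated-measures ANOVA for 12-month change relies on sphericity; if correlation falls with time and nothing corrects for it, the 12-month interval is too narrow and the F test mildly liberal

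*Protocol article*

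**What the plan says.** The Statistical analysis section of the protocol article names the method: "Additional analyses will be completed with a one-way repeated measures analysis of variance (ANOVA) to test for differences in physical activity and sedentary behaviour". The result is to carry a 95% interval, and the analysis is confined to the Australian cohort. The Outcome measures section makes accelerometer-measured sedentary behaviour and physical activity the main outcomes. The Discussion says that the repeated visits serve to determine short and medium-term change. No other test of change is described.

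The abstract gives the schedule: "Outcome measures will be taken at baseline (commence CR), 6 weeks (complete CR), 6 and 12-months". The Design section agrees: "participants will be assessed again within 2 weeks of finishing the 6-week phase II CR program, and at 6 and 12-months".

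On scale, the Statistical analysis section says: "The number of minutes per day spent in sedentary behaviour will be calculated using standard count-based intensity threshold values of counts per minute". It names no transformation and rules none out. It does not mention a sphericity correction and does not say which error term the interval uses. Missing follow-up values are replaced by the last observed value.

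For moderate-to-vigorous activity (MVPA), the only level given is a Background figure from cited work: "only 8.4 min per day of moderate-to-vigorous intensity physical activity (MVPA) is achieved in the first 12 months following diagnosis of CHD". The article gives no standard deviation, skewness or between-visit correlation.

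**The concern.** A one-way repeated-measures ANOVA has one error term for all visit comparisons. That term is right for every comparison only when the variance of the difference is the same for each pair of visits. Baseline and 6 weeks are close together, and baseline and 12 months are far apart. If correlation falls with the gap, the 12-month difference varies more than the pooled term implies and the 6-week difference varies less.

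The F test would then reject too often unless corrected. Any interval built on the pooled error would be too narrow for the 12-month change and too wide for the change over the rehabilitation programme. These are the medium-term and short-term changes that the study sets out to describe. The point applies to sedentary and activity measures alike.

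A secondary matter concerns MVPA only. A quantity that cannot go below zero and averages a few minutes a day is likely to be right-skewed, so an analysis of mean minutes may be less sensitive than one on the log scale.

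**Working it through.** **The plan's own figure.** The only sample size in the article is for the regression: f² = 0.5, "given a maximum of 10 predictor variables including potential confounders", α = 0.05, power 0.95. With noncentrality λ = f²·n = 0.5 × 59 = 29.5 and degrees of freedom 10 and 48, power is 0.952 at n = 59 and 0.947 at n = 58. So n = 59 reproduces. It does not size the ANOVA, for which no power is stated. With 75 recruited and 25% lost, 75 × 0.75 = 56 remain.

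**Formulae.** With equal variance σ² at each visit, a difference between visits i and j has variance 2σ²(1 − ρ_ij). The ANOVA error has expectation σ²(1 − ρ̄), where ρ̄ is the mean of the six correlations. The ratio of pooled to true standard error is therefore √[(1 − ρ̄)/(1 − ρ_ij)]. Coverage is about P(|t| ≤ 1.97 × ratio), with t on n − 1 degrees of freedom.

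**Steeper decline (assumed).** Visits at 0, 6, 26 and 52 weeks, ρ = r^(gap/26), n = 59. For r = 0.5:

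- The six correlations are 0.852, 0.500, 0.250, 0.587, 0.293 and 0.500, so ρ̄ = 0.497 and 1 − ρ̄ = 0.503.
- Baseline versus 12 months: √(0.503/0.750) = 0.82, and 1.97 × 0.82 = 1.61, so coverage is about 0.89.
- Baseline versus 6 weeks: √(0.503/0.148) = 1.84, so coverage is about 0.999.

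| r at 26 weeks | epsilon | F test, uncorrected type I error | SE ratio, 12 months | coverage, 12 months | SE ratio, 6 weeks | coverage, 6 weeks |
|---|---|---|---|---|---|---|
| 0.5 | 0.695 | 0.070 | 0.82 | 0.889 | 1.84 | 0.999 |
| 0.7 | 0.636 | 0.070 | 0.79 | 0.874 | 2.00 | >0.999 |
| 0.8 | 0.611 | 0.077 | 0.77 | 0.868 | 2.07 | >0.999 |
| 0.9 | 0.588 | 0.078 | 0.76 | 0.862 | 2.14 | >0.999 |

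With n = 75 the type I error is 0.067 to 0.078. A Greenhouse-Geisser correction brings it to about 0.045 to 0.054 (log scale).

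**Milder decline (assumed).** ρ = base × exp(−gap/range), visits at 0, 1.4, 6 and 12 months, n = 56. With correlation about 0.7 to 0.8 at 6 weeks and 0.2 to 0.6 at 12 months, epsilon is about 0.76 to 0.86 and type I error about 5.1 to 6.4%. Coverage is about 90 to 91% at 12 months and 99% at 6 weeks. Still weaker decline, with epsilon up to 0.91, gives 91 to 92% and 98 to 99%.

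**Equal correlations, same visit times.** With every ρ at 0.6, the ratio is √(0.4/0.4) = 1, epsilon is 1 and coverage is about 95%. With lognormal data (CV 0.8 to 1.3) and equal correlations, simulated coverage at n = 59 is 95.0 to 95.2% with pooled error and 95.1 to 95.7% with paired error.

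**MVPA scale (assumed lognormal, mean 8.4, multiplicative change).** Four-visit ANOVA, n = 59, Greenhouse-Geisser corrected, effect sized so that the log analysis has about 80% power:

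| CV | power on raw minutes | loss, points |
|---|---|---|
| 0.3 | 76–78% | 3–5 |
| 0.45 | 70–72% | 8–10 |
| 0.6 | 63–68% | 12–16 |
| 0.8 | 53–60% | 20–28 |
| 1.0 | 45–52% | 28–36 |
| 1.3 | 34–42% | 38–45 |

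A two-visit paired comparison (n = 56, 40% rise, between-visit correlation 0.5) gives 0.99 on raw minutes against 1.00 on the log scale at log-SD 0.5, and 0.33 against 0.60 at log-SD 1.1. A loss of about 20 points corresponds to one assumed spread among many.

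**The case against.** The strongest reply is that the harm is built on silence. The article does not say that MVPA is analysed in raw minutes, that no sphericity correction will be made, or that intervals use one pooled error. A condensed article commonly leaves these details to the full protocol or analysis plan. That stands, and it is why the figures above are conditional. It does not remove the point, because the ANOVA itself is a stated choice and a better method is available at little cost.

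A reader might infer that the unequal visit spacing invalidates the ANOVA. It does not. Visit enters as a factor, equal spacing is not assumed, and the same schedule gives correct intervals under equal correlations. The declining pattern is an assumption, and with the rehabilitation programme falling between the first two visits the true pattern could differ.

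A reader might also infer that the plan forfeits about 20 points of power for MVPA. The article supplies no spread or correlation from which that could be derived, and the 8.4 min/day is background from other studies, not a planning value for this cohort. Nor does skew by itself spoil the interval for mean change.

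Mean minutes are also the natural scale: the guideline is set in minutes, and 150/7 = 21.4 min/day. A log analysis answers a different question and needs a rule for zeros. A back-transformed log(x + 1) difference is not a true ratio of minutes. These objections stand, so the log analysis belongs beside mean minutes and should not replace them.

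Finally, none of the calculations models the carrying forward of last values, which would alter both effects and correlations. That is a separate matter.

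**Conclusion.** The point holds conditionally. If between-visit correlation falls with time, and no correction or contrast-specific error is used, the F test rejects about 5 to 8% of the time at a nominal 5%. That inflation is modest. The intervals matter more: about 86 to 91% coverage for baseline versus 12 months (nearer 92% under the weakest decline examined) and about 99% or more for baseline versus 6 weeks. Under equal correlations there is no error.

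These results rest on assumed correlation patterns, equal variances across visits and a pooled error term that the article neither states nor excludes. For MVPA, right skew is likely given "only 8.4 min per day of moderate-to-vigorous intensity physical activity (MVPA) is achieved", but any gain from a log scale lies anywhere from roughly 0 to 45 points across the assumed spreads and cannot be quoted as a fixed number.

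**What to change.** Replace the one-way repeated-measures ANOVA with a mixed model for repeated measures, with visit as a factor and an unstructured covariance. With four visits this needs 4 variances and 6 covariances, 10 parameters in all. Take each visit contrast and its 95% interval from that contrast's own standard error. This stays valid whether or not correlation declines. If the ANOVA is kept, specify a Greenhouse-Geisser corrected F test and paired standard errors for the contrasts.

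For MVPA, keep mean minutes as the main presentation and add a log-scale sensitivity analysis with a stated rule for zero minutes, reported as such. State no fixed power gain for it.

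A mixed model uses every observed visit without filling in missing ones, so the carry-forward sentence would need to be reconciled with it.

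The cost is a change of wording and slightly more analysis work. No new data or participants are needed.
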